**Fidelity—training**						
CHW-EF (10)	CHW enrolment and ID form	Field supervisors	CHWs	At enrolment, prior to initial training	Training (quantity/exposure)	Lists CHW names, sex, age, education, years working as CHW, residence and contact info, in enrolment/consent dates, prior trainings per content area and self-rated competency, if CHW has previously facilitated group discussion to lay audience (#), topics CHWs want covered during the training and skills they want to build, CHW ID, group ID supporting, village name, supervisor name
CHW-TAR (11)	CHW Ttraining attendance register	Training lead facilitator	CHWs	At each day of training	Training (structure/quantity)	Staff ID (lead facilitator, co-facilitator (s)), venue location, dates and number of days, trial arm ID, trial arm name, district, CHW ID, CHW name
CHW PPT (12)	CHW pre- and post-training tests, by topic	Field supervisors	CHWs	Before and after each training	Training (quality)	CHW knowledge, attitudes, and skills on topics they will facilitate; feedback on satisfaction with the training
TEF (13)	Training evaluation form	CHWs, field supervisors, M&E officers	CHWs, field supervisors, M&E officers	After each training (main training, refresher trainings)	Training (quality)	Satisfaction with training (e.g., enough space, organization, quality of facilitation, quality of materials, time allocation including for interaction and sharing, number of topics covered) as well as what was learned the most, topics that were challenging, and recommendations for improving the training
TERM (8)	Study termination form	Field supervisors	CHWs	If/when CHW terminates from study	Training (quantity and exposure)	ID # of dropped; CHW, date dropped; reason for termination. Note: will use the same form as the participant TERM form.
**Fidelity—supervision**						
CMR (14)	CHW meeting report	Field supervisors	CHWs	During/after each review/mentorship meeting	Supervision (structure, quality, and quantity), barriers and facilitators; community demand (i.e., community-level actions taken)	Date of the meeting, duration of the meeting, content covered during the quarterly meeting, e.g., summary of progress, breakthrough opportunities; barriers and facilitators to implementation from CHW and FS perspectives—what is working well, challenges and recommendation for overcoming barriers, areas needing improvement
PMM (15)	Program manager monthly report	Field supervisors	PM and field supervisors	During/after each monthly review/mentorship meeting	Supervision (structure/quantity, quality)	Date completed/month reported on, staff changes, communication with government entities, any partnerships that developed/occurred) sessions covered that month, CHW completion of sessions, major successes, challenges encountered by FS team, lessons learned, QI changes made (if yes, attach form), calendar events that month (if yes, attach form), other issues to report

#### Data management

Data will be collected electronically using hand-held tablet devices using the Open Data Kit platform. The data collection team will be trained by the EFFECTS research team. The first training will build an understanding of the study’s underlying concepts as well as the study methodology. Both logic and quality measures will be revised during data collection training.

Data will be uploaded daily from the tablets to a password-protected database on a secure cloud-based storage system that is managed by AAPH. Study coordinators will keep logs of supervision to further ensure data quality. Data quality management will be at multiple levels; first, data collection modules are tested rigorously and piloted prior to baseline data collection. Second, initial data checks, initial data cleaning, and backup storage will be conducted weekly throughout the course of data collection. Finally, weekly calls will be established with the evaluation coordinator, data manager, and research co-investigators to discuss and resolve any emerging issues in the field or data collection process. All data transmission will be done using secure channels.

#### Analysis plan

Analyses will be based on the intention-to-treat principle. The main analyses will test for differences-in-differences for primary and secondary outcomes across the 12 months of intervention. For each outcome, we will fit a generalized linear mixed model with district, study arm, time point of evaluation (baseline, midline, or endline), and interaction between study arm and time point of evaluation as fixed effects. All models will adjust for clustering within villages and repeated measurements on individuals and households. All hypothesis tests will be two-sided with a 0.05 significance level.

For each outcome, we will specifically ask four research questions, using contrasts to test for significant differences-in-differences. The first research question tests whether engaging families through any intervention affects the specified outcome beyond changes observed among families receiving standard of care. To answer this question, the contrast will compare the average change from baseline to endline in the four intervention arms to the corresponding change in the control arm. The second research question tests whether engaging both mothers and fathers affects an outcome differently than engaging mothers alone. To answer this question, the contrast will compare the average change from baseline to endline in the two arms that engage both parents to the corresponding average change in the two arms that engage only mothers. This provides a difference-in-difference estimate for the effect of father engagement. The third research question tests whether delivering bundled nutrition and parenting content affects an outcome differently than delivering nutrition content alone. To answer this question, the contrast will compare the average change from baseline to endline in the two arms that deliver bundled content to the corresponding average change in the two arms that deliver only nutrition content. This provides a difference-in-difference estimate for the effect of bundling nutrition and parenting content. Finally, the fourth research question tests whether the effect of father engagement depends on which content is delivered or, similarly, whether the effect of bundling nutrition and parenting content depends on whether or not fathers are engaged. Statistically, this is a test for interaction between father engagement and bundling content. To answer this question, we first estimate the change from baseline to endline in the couples’ nutrition arm compared with the corresponding change in the mothers’ nutrition arm; this estimates the effect of father engagement when nutrition content is delivered. We then estimate the change from baseline to endline in the couples’ bundled content arm compared with the corresponding change in the mothers’ bundled content arm; this estimates the effect of father engagement when bundled content is delivered. The contrast that answers the fourth research question compares these two estimates: the effect of father engagement when nutrition content is delivered vs. the effect of father engagement when bundled content is delivered.

Secondary adjusted analyses will also be conducted using the generalized linear mixed models specified above along with additional outcome-specific predictors (e.g., household wealth or child sex and age) hypothesized to influence the outcome. The large dataset will also allow for additional analyses, such as investigation of potential modifiers and mediators of intervention effects. Potential effect modifiers that might influence the degree of intervention impacts on child nutrition and development outcomes include socioeconomic status, household composition, and intervention process-related factors (e.g., attendance, fidelity, quality of implementation). Potential mediators include maternal and paternal knowledge and caregiving practices for nutrition and ECD, maternal and paternal psychosocial well-being and social support, quality of couples’ relationships, allocation of household resources, and food access.

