### Randomization and recruitment

#### Village selection

Eighty study villages in the two districts of Musoma Rural and Butiama were randomly selected with stratification by district and randomly allocated with equal probability and in equal numbers to one of the five EFFECTS study arms. In each district, all villages were listed (68 in Musoma Rural and 58 in Butiama). In Musoma Rural, which borders Lake Victoria, all villages that had a coastline were identified and removed from this sampling frame of villages. We therefore excluded from our study communities (and households within those communities) where fishing could be an important source of livelihood. We believed that the roles of fathers, in particular in childcare, could be different than in communities and households were fathers were not engaged in fishing as a livelihood, as fishing in the region can take men away from their households for extended periods. Exclusion of coastal villages resulted in a sampling frame with 39 villages in Musoma Rural and 58 villages in Butiama. In Musoma Rural, all 39 villages were selected for the EFFECTS study, as we had originally intended to have 40 villages/district. In Butiama, 41 villages were selected using simple random sampling to achieve our target of 80 participating villages. A further set of villages in Butiama were randomly selected as backup villages, in case any of the 80 selected villages did not enroll in or dropped from our study. These backup villages were listed in random order and were used in that order to replace study villages.

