#### Village and sub-village randomization

In September 2018, the field team organized combined sensitization and randomization meetings with District Nutrition Officers, Ward Executive Officers, 41 Village Executive Officers (VEOs) from Butiama, and 39 VEOs from Musoma Rural to publicly and transparently select at random their intervention assignment and to select at random one sub-village per village to participate in the study. Interventions were implemented in only one sub-village per village to minimize participants’ walking distance to peer group meetings. The VEOs actively participated in the random allocation of their village to a study arm by selecting a piece of paper from an opaque bag upon which was written a letter which corresponded to one of the five study arms. All pieces of paper were identically sized and shaped. To achieve balance among the treatment arms across districts and to facilitate intervention implementation, eight villages per district were assigned to each intervention. This resulted in seven control villages in Musoma Rural and nine control villages in Butiama.

After villages were randomized to one of five treatment arms, the field team worked with each VEO, who randomly selected one sub-village out of all sub-villages in his or her village for participation in the study. Village leaders were asked to bring a list of all sub-villages to the randomization exercise; the list of sub-villages that each of the village leaders brought with them was received and reviewed together with a field study team member. Each village leader worked with two field team members to write the names of each sub-village on a small identically shaped and identically sized piece of paper. These pieces of paper were placed in an opaque bag and the village leader randomly selected pieces of paper from the bag. The first selected sub-village was the sub-village in which EFFECTS will implement the respective intervention. The other sub-villages were documented in the order that they were selected and would serve as backup sub-villages in that order. During these randomization processes, it was discovered that one village in the sampling frame did not exist and one village was a sub-village. It was also discovered that two villages/sub-villages, one in each district, were not reachable during the rainy season. Backup villages were used to replace these villages.

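### District is modelled only as a main effect, so the baseline-to-endline contrasts gain nothing from balancing on it, and the published district counts describe the initial draw, not the villages finally enrolled

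*Protocol article*

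**What the plan says.** **Model.** Under Analysis plan, each outcome gets a "generalized linear mixed model with district, study arm, time point of evaluation (baseline, midline, or endline"). The only interaction listed is that of arm with time: "and interaction between study arm and time point of evaluation as fixed effects". Clustering within villages and repeated measurements are adjusted for. No district-by-time term is listed.

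**Contrasts.** The same section poses four questions, "using contrasts to test for significant differences-in-differences". Numbered in the protocol's order:
- RQ1: all four intervention arms against control.
- RQ2: both parents engaged against mothers alone.
- RQ3: bundled content against nutrition only.
- RQ4: the interaction between father engagement and bundling.

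Each compares changes from baseline to endline.

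**Allocation.** Under Village selection, the 80 villages were "randomly selected with stratification by district and randomly allocated with equal probability and in equal numbers". All 39 eligible Musoma Rural villages and 41 of the 58 Butiama villages were taken. The reserve was drawn in one district: "A further set of villages in Butiama were randomly selected as backup villages". Under Village and sub-village randomization, "eight villages per district were assigned to each intervention", and for the control arm: "This resulted in seven control villages in Musoma Rural and nine control villages in Butiama".

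**Replacements.** The same section reports that one listed village did not exist, that one was really a sub-village, and that "two villages/sub-villages, one in each district, were not reachable during the rainy season". Backup villages took their places. The Household selection section adds that seven more villages, overlapping with another organisation's nutrition project, were replaced from the backup list, with arm and sub-village again drawn at random. Their districts are not given.

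**The concern.** Balancing allocation on a factor pays off in precision when the analysis accounts for that factor in the quantity being estimated. Here that quantity is change over time, and district is entered only as a constant shift in level. If the two districts follow different trends, through season, markets or the March 2020 disruption for example, that difference stays in the village-by-time error. The design has removed it from the comparison, but the standard error still includes it.

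The second part concerns the balance itself. The eight-and-eight counts are what keep a district trend out of RQ2 to RQ4 when no district-by-time term is fitted. If villages in one district were replaced by villages in the other, that protection is weakened by an amount the reader cannot determine from the article.

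**Working it through.** **1. The plan's own counts.** Musoma Rural: 4 x 8 + 7 = 39. Butiama: 4 x 8 + 9 = 41. Total 80. The stated draw is internally consistent.

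**2. Does the district main effect cancel?** Write the expected outcome in district d, arm a, time t as mu + delta_d + alpha_a + tau_t + (alpha tau)_at. The change from baseline to endline is tau_2 - tau_0 + (alpha tau)_a2 - (alpha tau)_a0, and delta_d is gone. Generalized least squares on simulated data confirms this (80 villages, 12 households, 3 visits; assumed variances: village 0.07, village-by-time 0.03, household 0.3, residual 0.6). On complete data, adding the district main effect left all four estimates and standard errors identical to five decimals: SE 0.1118 for RQ1, 0.1000 for RQ2 and RQ3, 0.2000 for RQ4. With 10% endline dropout, estimates moved by less than 0.002 and standard errors did not change. Under a non-identity link the cancellation is not exact.

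**3. Cost in precision.** From the Sample size/power calculation section: SD 1 food group, ICC 0.1, 12 households per village, 10% loss, hence 12 x 0.9 = 10.8 per village. Assumed: correlation of village effects across visits (CAC) 0.6 to 0.8, correlation of household deviations across visits (r) 0.1 to 0.2, and a district difference in change D of 0.25 to 0.5 food groups.

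- Within-district variance of a village's mean change: 2 x 0.1 x (1 - CAC) + 2 x 0.9 x (1 - r)/10.8.
- Smallest (CAC 0.8, r 0.2): 0.040 + 0.133 = 0.173. Largest (CAC 0.6, r 0.1): 0.080 + 0.150 = 0.230.
- Variance added when district-by-time is left out: D² x (39/80) x (41/80) = 0.0156 at D = 0.25 and 0.0625 at D = 0.5.
- SE ratio = sqrt(1 + added/within):

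| D | within 0.230 | within 0.173 |
|---|---|---|
| 0.25 | 1.03 | 1.04 |
| 0.5 | 1.13 | 1.17 |

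Under the stated balance, RQ2 to RQ4 do not vary with the district trend, so this excess is in the reported SE and not in the true one. By normal approximation, the actual two-sided type I error is 2 x P(Z > 1.96 x ratio): 4.1-4.3% at D = 0.25 and 2.2-2.7% at D = 0.5. An effect that should have 80% power has Phi(2.80 - 1.96 x ratio): 77-78% and 70-72% respectively.

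**4. Confounding under the stated draw.** The imbalance is the difference in Musoma share between the compared arms. RQ1: 8/16 - 7/16 = 1/16 = 0.0625, which at D = 0.5 is 0.031 food groups. RQ2, RQ3 and RQ4: 0.

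**5. Counts after replacement.** Replacements: 4 + 7 = 11, which fits within the 58 - 41 = 17 remaining Butiama villages. No Musoma village was left to act as a backup. Of the first four, one was in Musoma, one was in Butiama and two are unstated; the seven later ones are unstated. Musoma losses therefore lie between 1 and 1 + 2 + 7 = 10. The final split is between 38/42 and 29/51.

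**6. What one lost Musoma village does.** Each contrast has its own weight per village:
- RQ1: 1/4 x 1/16 = 1/64 in an intervention arm, 1/16 in control. Losing an intervention village reduces the imbalance to 31/64 - 7/16 = 0.047. Losing a control village raises it to 8/16 - 6/16 = 0.125.
- RQ2 and RQ3: 1/2 x 1/16 = 1/32, so 0.031.
- RQ4: 1/16, so 0.0625.

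If all ten possible losses fell at random across arms, the simulated mean absolute share difference would be 0.075, 0.062, 0.062 and 0.123 for RQ1 to RQ4. At D = 0.5 that is about 0.04, 0.03, 0.03 and 0.06 food groups.

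**The case against.** Entering the balancing factor as a fixed effect is ordinary practice, and under the stated draw RQ2 to RQ4 are balanced on district whether or not district-by-time is fitted. Both statements stand. A reader might infer that the stratified design is ignored altogether, or that the father-engagement and bundling estimates are biased. The text supports neither: district is in the model, and the eight-and-eight draw protects those point estimates. What is lost is only the precision gain in the change contrasts.

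The precision loss also rests on a trend difference that the protocol nowhere states. The upper value of 0.5 exceeds the trial's own detectable difference of 0.43 food groups. With no divergence there is no loss, and any loss makes the tests conservative. The calculation further requires village-by-time variation to be in the model, whereas the article says only that clustering within villages is adjusted for. These points also stand, so the standard errors cannot be called wrong as a fact.

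On the counts, a reader might call the stated balance false. It can fairly be read as the September 2018 draw, and the later replacements are openly reported. The phrase covering villages or sub-villages leaves a narrow possibility that the unreachable Musoma unit was replaced within its own village, although the text says that backup villages were used. The seven later replacements were themselves randomly allocated, so any imbalance from them is chance, not systematic bias. It would also be wrong to charge 1/16 per replaced village to every contrast: that weight applies to RQ4 and to control villages in RQ1 only, and in RQ1 an intervention-arm loss partly offsets the 7/9 control split.

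**Conclusion.** The point holds in a limited form. District does no work in the four change contrasts: exactly so for an identity link with complete data, nearly so with dropout, and only approximately under other links. Given a district trend difference of 0.25 to 0.5 food groups and modelled village-by-time variation, both assumed, the planned standard errors are about 3-4% to 13-17% too wide. The error is on the conservative side and costs power. The only imbalance in the stated draw affects RQ1, at about 0.03 food groups for a trend difference of 0.5, against a standard error near 0.11 under the variances assumed above.

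Read literally, the final split is at most 38 Musoma to 42 Butiama, so the published counts by arm cannot describe the analysed villages. The size and direction of any resulting imbalance are unknown, because neither the arms nor most of the districts of the replaced villages are given. The documents show no material bias in a primary estimate, and the sample size calculation is not affected.

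**What to change.** Add the district-by-time-point interaction as a fixed effect in the primary model for every outcome, coding each analysed village by its actual district and not by the district of the village it replaced. This takes two fixed-effect degrees of freedom. In the simulated check, with the stated balance and complete data, it left the RQ2 to RQ4 estimates and standard errors unchanged and moved the RQ1 standard error only from 0.1118 to 0.1119.

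In the Village and sub-village randomization section, label the eight-and-eight and seven-and-nine counts as the initial draw. Add one sentence or a small table with the final number of villages by district and arm after all replacements, and say whether the unreachable Musoma Rural unit was replaced by a Butiama village. No new data are needed.

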### Trial design

This cluster-randomized controlled trial will use a 2×2 factorial design, plus a local standard of care control group, to evaluate the effectiveness of EFFECTS interventions. There will be a total of five study arms. Eighty villages will be randomly assigned in equal numbers to one of the five arms:Nutrition behavior change intervention delivered through peer groups of mothersNutrition behavior change intervention delivered through peer groups of both mothers and fathersNutrition and parenting behavior change intervention delivered through peer groups of mothersNutrition and parenting behavior change intervention delivered through peer groups of both mothers and fathersControl arm receiving local standard of care

The EFFECTS study design will enable the individual and combined comparison of two strategies: (1) a bundled nutrition and parenting curriculum compared to a nutrition only curriculum and compared to the local standard of care and (2) the active engagement of fathers in both a bundled nutrition and parenting curriculum and a nutrition only curriculum compared to delivering these curricula to only mothers and compared to the local standard of care. All participating households in the five study arms will be assessed at baseline (prior to the start of any interventions), after 6 months of intervention (“midline” or “6 months”), and after the completion of 12 months of intervention (“endline” or “12 months”). Cluster randomization, rather than individual randomization, will be used as interventions will be delivered to peer groups of parents, rather than individual parents. Randomization at the village level also reduces the likelihood of spillover effects, in which knowledge gained through behavior change interventions is shared with individuals assigned to a different study arm, as families are less likely to interact with others in a different village than in the same village. Given the nature of these community-based interventions, blinding will not be possible except for outcome assessors, who will not be made aware of villages’ assignments to study arms.

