### Outcomes

Table 1 lists the study’s primary and secondary outcome measures. The primary outcome measures are (1) child dietary diversity measured as the number of food groups out of eight consumed by the child in the preceding day (24 h) [32] and (2) child development, comprising child cognitive, language, motor, and socioemotional development, directly assessed using the Bayley Scales of Infant and Toddler Development, Third Edition (BSID-III), which has been previously adapted and validated for use in Tanzania [33]. Outcomes are assessed on all participating households at baseline and after 6 and 12 months of intervention (detailed in Table 2 per SPIRIT Guidelines).

**Table 1 Tab1:** Primary and secondary outcomes in the EFFECTS trial and timing of assessment

Outcomes	Measures	Baseline	6 months	12 months
Primary outcomes				
Child dietary diversity (24 h)	Number of food groups out of eight food groups consumed in the previous day (24 h) by children aged 6+ months, based on WHO guidelines	x	x	x
Child development	Cognitive, language, motor, and socioemotional development, assessed using the Bayley Scales of Infant and Toddler Development, Third Edition (BSID-III)	x	x	x
Secondary outcomes	Primary, secondary, and process outcomes and measures			
Child dietary diversity (7 days)	Number of food groups out of eight food groups consumed in the previous 7 days by children aged 6+ months, based on WHO guidelines	x	x	x
Child nutritional status	Height-for-age *z*-scores (HAZ) and weight-for-height *z*-scores (WHZ), based on WHO Multicentre Child Growth Standards	x		x
Minimum meal frequency	Proportion of children aged 6+ months (breastfeeding and non-breastfeeding) meeting minimum meal frequency guideline based on the WHO-UNICEF tool	x	x	x
Household allocation of animal source foods	Change in proportion of children (aged 6+ months), mothers, and fathers consuming eggs or meat the previous day given that at least one of the three consumed eggs or meat the previous day	x	x	x
Maternal and paternal infant and young child (IYCF) knowledge and practices	Caregiver knowledge and practice questionnaire regarding age-appropriate infant and young child (1) breastfeeding and support and (2) complementary feeding, measured using an adapted version of the the WHO-UNICEF tool	x	x	x
Responsive feeding practices	Maternal responsive feeding behavior tool	x		x

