### Sample size/power calculation

This study will enroll a total of 960 households, or 192 households per arm (12 households per village and 16 villages per arm). While some analyses will involve pooling of study arms (for example, pooling of the two mothers-only arms and of the two arms engaging both mothers and fathers to estimate the main effects of fathers’ engagement), the statistical power calculation for the primary outcome of child dietary diversity conservatively assumed pairwise comparison of individual study interventions. Assuming a standard deviation of 1 food group and an intracluster correlation coefficient of 0.1, this design has 80% power to detect a difference of 0.43 food groups between any two study interventions. Similarly, this design has 80% power to detect a 5-point difference in each of the BSID composite scores. The sample size calculation allows for a 10% loss to follow-up.

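### The primary dietary-diversity model leaves out child age, although age decides who has a baseline value; adding it would be a small, nearly free gain in precision

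*Protocol article*

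**What the plan says.** The Analysis plan section of the protocol article sets one generalized linear mixed model for every outcome. Its fixed effects are district, arm, time point and the arm-by-time interaction, with allowance for village clustering and repeated measurements. The research questions are answered by between-arm contrasts of change; for the first, "the contrast will compare the average change from baseline to endline in the four intervention arms to the corresponding change in the control arm". Child age appears only in the secondary adjusted analyses, which refit the model "along with additional outcome-specific predictors (e.g., household wealth or child sex and age) hypothesized to influence the outcome".

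Two other sections bear on this. The eligibility criteria admit children from birth to 18 months. Table 1 defines the primary dietary outcome as the number of food groups "consumed in the previous day (24 h) by children aged 6+ months". Three secondary outcomes in Table 1 carry the same age limit for the child: 7-day dietary diversity, minimum meal frequency and the child's share of animal source foods.

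**The concern.** Taken together, these rules mean that a child younger than 6 months at baseline contributes an endline value but no baseline value. The baseline mean in each arm comes from the older children and the endline mean from all of them. Age therefore determines who is in the baseline set, and the plan itself offers age as an example of a covariate expected to influence an outcome, but the primary model does not contain it.

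Two things are at stake. First, with complete baselines and a linear age effect, an age imbalance between arms appears at both visits and cancels in the change. Children without a baseline value have nothing to cancel against, so part of a chance imbalance reaches the treatment contrast. Second, a predictor that must be recorded anyway, because eligibility and the outcome definition both depend on it, goes unused in the primary estimate.

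**Working it through.** **1. The plan's own figure.** The Sample size section states: "Assuming a standard deviation of 1 food group and an intracluster correlation coefficient of 0.1". It concludes that "this design has 80% power to detect a difference of 0.43 food groups between any two study interventions". The Analysis plan adds: "All hypothesis tests will be two-sided with a 0.05 significance level". With 192 per arm in 16 villages and 10% loss, n = 172.8 per arm and 10.8 per village.
- Design effect = 1 + (10.8 − 1) × 0.1 = 1.98
- SE = √(2 × 1.98 / 172.8) = 0.151
- Detectable difference = (1.96 + 0.84) × 0.151 = 0.424; power at 0.43 = 81.1%
- With the design effect kept at 12 per village (2.1): 0.437 and 78.8%

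The stated 0.43 at 80% power is reproduced. It is an endline-type comparison that uses neither age nor baseline, so nothing below contradicts it.

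**2. Who lacks a baseline value.** The documents give neither an age distribution nor the time from enrolment to baseline. Assume ages uniform over 0–18 months at enrolment.

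| Lag to baseline | Share under 6 months | Per arm of 192 |
|---|---|---|
| 0 months | 6/18 = 33% | 64 |
| 3 months | 3/18 = 17% | 32 |
| 6 months | 0% | 0 |

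With no lag, mean age is 12 months in the baseline set and 21 months in the endline set. The baseline set followed for 12 months would average 24.

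**3. How much chance imbalance reaches the contrast.** The SD of a uniform age over 18 months is 18/√12 = 5.20. The chance SD of the difference in mean age, treating ages as independent within villages, is:
- two single arms: 5.20 × √(2/192) = 0.53 months
- two pooled pairs of arms: 5.20 × √(2/384) = 0.37 months

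Suppose one arm is 1 month older throughout (1–19 instead of 0–18 months). Its endline mean age rises by 1.0 month. Its observed baseline set becomes 6–19 months, so that mean rises from 12 to 12.5. The net is 0.5 month, before any borrowing by the mixed model. About half of the imbalance cancels and half remains.

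**4. Effect on precision.** The protocol's primary model was simulated 500 times per scenario, with village and child random intercepts, and fitted without age and with a linear age spline. Assumptions, none of them in the documents: uniform age, within-child correlation 0.3, no village-by-time variation, diet score rising linearly from 6 to 24 months and then flat. The ICC is 0.1 and the true effect 0.43. The last column is √(SE without² − SE with²), the SD of the shift that age imbalance causes.

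| Slope per month | Lag | SE without age | SE with age | Reduction | Power without → with | SD of shift |
|---|---|---|---|---|---|---|
| 0 | 0 | 0.1429 | 0.1429 | 0% | 85.3 → 85.3% | 0 |
| 0.05 | 0 | 0.1437 | 0.1429 | 0.6% | 84.9 → 85.3% | 0.015 |
| 0.10 | 0 | 0.1457 | 0.1429 | 1.9% | 83.9 → 85.3% | 0.028 |
| 0.15 | 0 | 0.1481 | 0.1429 | 3.5% | 82.7 → 85.3% | 0.039 |
| 0.10 | 6 months | 0.1305 | 0.1243 | 4.8% | 90.9 → 93.3% | 0.040 |

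These are for two single arms. For the pooled two-against-two contrasts with no lag, the SE falls by 0–2.7% (at slope 0.15, from 0.1066 to 0.1037).

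The no-lag shifts agree with step 3: 0.5 × 0.53 × slope gives 0.013, 0.027 and 0.040. In the last row no baseline is missing; there the gain comes from the assumed plateau at 24 months, which stops age from cancelling.

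**5. Bias.** The mean estimate was 0.434–0.435 with or without age, against a true 0.43. The Monte Carlo error of that mean is about 0.143/√500 = 0.006.

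**6. What age adjustment cannot do.** At slope 0.10 the SE without age is 0.146 with a third of baselines missing and 0.131 with none missing. Adding age to the first case brings it only to 0.143.

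**The case against.** The strongest reply is that the trial never tests a within-arm change. Its contrasts compare randomised arms, the shift in age mix is expected to be the same in each, and it cancels. That stands, and step 5 bears it out. A reader might infer that age-driven missing baselines defeat the mixed model's missing-at-random argument and so bias the primary result. The documents do not support this for the between-arm contrasts: the value is absent because the outcome is undefined at that age, and age at entry is unrelated to arm in expectation. The inference holds only for a within-arm change read as the change of one cohort.

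A reader might also multiply a 1-month imbalance by the full age slope. That treats the analysis as endline-only. In the planned contrast the figure is roughly halved, and a 1-month imbalance is about 1.9 chance SDs for two arms (1/0.53) and 2.7 for pooled pairs (1/0.375).

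Nor can a third of children be taken as the missing share. Household selection describes households losing eligibility before baseline, and Trial status says data collection tools were finalised only after enrolment was complete. Some lag is therefore likely, and the share may be well below a third.

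Finally, age-adjusted analyses are already planned, and a full analysis plan may fix the covariates. This weakens the point but does not remove it: the article fixes the primary model without age and names age only as an example among secondary covariates.

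**Conclusion.** The point holds as a minor efficiency matter. The primary dietary-diversity model omits a likely predictor that also determines who has a baseline value. The between-arm contrasts are unbiased in expectation. What is lost is some protection against chance age imbalance and a little precision: roughly 0–5% of the standard error and 0–3 points of pairwise power at 0.43, for assumed slopes of 0–0.15 food groups per month. The documents give no age distribution, no relation of diet to age and no enrolment-to-baseline lag, so the size cannot be fixed more closely. In every scenario tried, power without age stayed above 80%, and the stated detectable difference of 0.43 is not in question. When baselines are missing, their absence costs more precision than the omission of age.

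**What to change.** Prespecify child age at assessment, as a spline or in bands, in the primary model for 24-hour dietary diversity. Do the same for the other outcomes defined from 6 months: 7-day diversity, minimum meal frequency and the child component of animal source foods. Keep the model without age as a sensitivity analysis. State in one sentence how children under 6 months at baseline enter the change contrast, so that arm-level changes are not read as the change of a single cohort.

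The cost is a line or two in the analysis plan and a few degrees of freedom. No new data are needed. Naming the age term in advance also avoids a later choice between an unadjusted primary result and a loosely specified adjusted one. The change does not restore the missing baseline values.
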